The term ‘Detailing’ was originally coined to describe a form of educational outreach pioneered by the Pharmaceutical Industry through representatives promoting their products. Marketing and selling strategies are incorporated, tailored to the doctor’s personality, practice style and preferences. Acknowledging the usefulness of this approach in a commercial, for-profit sense, the methods have been applied to benefit the ‘not for profit’ sectors e.g. the National Health Service. This led to the terms ‘Public interest’ or ‘academic’ detailing, and the process of non commercial, short, face to face, in-service interactive education by a trusted outsider trying to promote evidence based choices among physicians. The median improvement in prescribing from this approach is estimated to be approximately 6% with a range from -4% to 17%, up to 1 year (Grimshaw 2004) although Avorn achieved a difference of 18% (Avorn 1983: see Table 1). Core features of this complex model are not well understood. There is no consensus or guidance on how narrow or wide the topic should be, or the relative efficacy of components e.g. written compared with face to face feedback. Frequency of contacts between pharmacist and prescriber vary between studies. Some suggest that eight, one hour sessions per practice are sufficient to effect prescribing change at practice level (Squires 1997), while others recommend meetings every 4 – 8 weeks, of one hour duration (Pilling 1998), but there is no consensus, partly because of the differences in context, content and delivery, topics, training of staff involved.

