**1.6.2 The case for improving Statin prescribing**

In response to growing acknowledgement of the benefits, their prescribing has increased more dramatically than most other medicines (Ramsay 2006; Bull 2003).However, this generates three linked questions:

1. Of those with established vascular disease, are all eligible patients receiving a statin at the right dose? If not, what can be done to improve uptake of adequate prescribing and dosing?

2. Can pharmacists based in practices turn their attention to improving uptake, through

a model of prescribing support?

3. Can this work be adequately described and tested, to ensure a robust answer to these questions?

Based on the review of prescribing support models described above, there are no ‘off the shelf’ interventions to ensure maximal uptake of statin prescribing guidance. This argues for innovation in the design and application of a novel intervention.

From the evidence described above, there is a robust case for prescribing statins for patients with established vascular disease. Prior to HPS, the evidence was less convincing for such a wide spectrum of patients. Publication of HPS led to reappraisal of statin guidelines and together, this is likely to account for the recent increase in statin prescribing, which has surpassed increases in any other risk reducing medicines (Bull 2003; Ramsay 2006).

This finding has important implications for the design of a trial testing an intervention to help increase statin prescribing: usual care (due to passive dissemination of guidance) is likely to improve over time and this should be factored into the power calculation. That prescribing increases over time, coinciding with the publication of new evidence, is not a new finding. Calvo and Rubinstein evaluated prescribing pre- and post- publication of successful drug trials. They monitored the incidence of new prescriptions written by physicians in primary care in a 6 month period before and after publication of trials of the following drugs: alendronate, metformin, alpha1-blockers and finasteride. Among their findings was a clear, statistically significant temporal association between prescribing and the publication of the new evidence (Calvo 2002).

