However, the literature review gave a convincing account of there being shortfalls in the prescribing and use of lipid lowering agents (ASPIRE steering group 1996; Campbell 1998; Siegel 2000; Ramsay 2006; Sempos 1993; Clinical Quality Improvement Network Investigators 1995; Northridge 1994; McBride 1998; Sueta 1999; McCormick 1999; Aronson 2006; De Wilde 2003; Primatesta 2000; Whincup 2002; Minhas 2004; Smith 2001; Missouris 2001; Sloan 2001; Frolkis 1998; Hoereger 1998; Reid 2002; Majeed 2000; Fernie 2006; Pearson 2000). Many of these papers reported suboptimal statin prescribing after the publication date of the HPS. The studies varied in design, methodology, sample characteristics, country of origin and severity of cardiovascular disease. There were biases and confounding inherent in most of these due to the absence of a comparator group but the consistent finding was there being considerable scope for improvement in the identification of patients eligible for treatment, statin prescribing in comparison with the evidence base, achievement of target statin doses and achievement of target cholesterol levels.

In EUROASPIRE II, the investigators’ found half of those eligible were receiving statins and of those receiving them, half were reaching the target of 5mmol/l (EUROASPIRE II 2001). A subsequent comparison of EUROASPIRE studies I and II led to the assertion that there was a collective failure across Europe, of practice to achieve the substantial potential among patients with CHD to reduce the risk of recurrent disease and death. Approximately 60% of those patients interviewed across the nine participating countries were prescribed statins between 1999 and 2000 (EUROASPIRE I and II group. 2001). Since then, the introduction of the New General Medical Services (GMS) contract has proved that at least 60% of patients with CVD and diabetes can achieve total cholesterol levels below 5mmol/l (QOF Achievement Data 2005). However, it is not known if there can be any further improvement in uptake beyond the 60% audit target set by the GMS contract, or how many more patients would start and continue to take newly prescribed statins if the health care professionals adopted the best available implementation techniques, informed by implementation research. It is likely that there will remain a significant number of patients who will not take their statin out of choice, even if it were prescribed.

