**3.5 Statistical analysis**

Pilot work found 50% of patients to have cholesterol controlled with an intraclass correlation (ICC) of 0.4. Assuming that data for 40 patients per practice would be collected, we estimated that approximately 20 practices (10 per group) would be required to detect an increase in cholesterol control to 90% in intervention practices. We anticipated a high practice dropout rate due to the length and intensity of the intervention. We, therefore, invited 49 practices to participate.

Analysis will be by intention to treat. Descriptive statistics for continuous variables will be presented as mean and standard deviation and for categorical variables, as frequencies and percentages. Baseline analysis will compare participating with non-participating practices, SOS with UC practices, and single handed with group practices. Patient level data will not be collected for non-participating practices. Summaries will use continuous and categorical variables, as appropriate. Practice-level data (e.g. number of GPs, list size) will be compared using the Wilcoxon-Mann-Whitney test, or, for comparisons between SOS and UC practices, using the Wilcoxon Signed Rank test within pairs of practices.

Due to the non-normal distribution of cholesterol levels, a log-transformation will be applied. Patient level data will be analysed at the individual level for greater power.

Linear and logistic regression models will be used to test for differences in the primary and secondary outcomes between the two intervention groups. These models will be adjusted for practice pair to account for the matching at randomisation. Results will be presented as intervention effect or odds ratio, 95% confidence interval and p-value. Secondary analyses will be carried out to investigate the sensitivity of the results to adjustments for age and sex. A sensitivity analysis, adjusting for any statin prescribing at follow up, will be carried out for the primary outcome to assess whether the treatment effect can be explained by increased statin prescribing.

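### The sample size holds usual care at the pilot 50%, although the protocol says its expected improvement should enter the power calculation

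*Protocol*

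**What the plan says.** The sample size paragraph stands at the start of protocol section 3.5. It opens with the pilot result: "Pilot work found 50% of patients to have cholesterol controlled with an intraclass correlation (ICC) of 0.4". It continues: "Assuming that data for 40 patients per practice would be collected", and arrives at the requirement that "approximately 20 practices (10 per group) would be required to detect an increase in cholesterol control to 90% in intervention practices". The comparison is therefore 50% against 90%. The paragraph then expects heavy practice dropout because the intervention is long and intense, and gives this as the reason for inviting 49 practices. It gives no significance level, sidedness or target power. The design effect formula, D = 1 + ρ(m – 1), is in section 3.4.

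Section 1.6.2 discusses the rise in statin prescribing after new evidence and guidance. It draws a design lesson for a trial of this kind: usual care "is likely to improve over time and this should be factored into the power calculation". The same section reports that the new GMS contract "has proved that at least 60% of patients with CVD and diabetes can achieve total cholesterol levels below 5mmol/l", and calls 60% the contract's audit target. Section 3.3 places outcome assessment 1.4 to 2.2 years after randomisation (mean 1.7).

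**The concern.** The protocol sets itself a rule in section 1.6.2 and does not apply it in section 3.5. A control rate fixed at the pilot value assumes that usual care stands still for about 1.7 years, while the rationale says that it will not. If usual care improves and the intervention rate remains 90%, the difference shrinks and 20 practices carry less power than the paragraph implies. With an intraclass correlation as high as 0.4, power depends almost entirely on the number of practices, so collecting more patients per practice would recover little.

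Because alpha and power are missing, a reader cannot see what the figure was meant to deliver or how sensitive it is to the control rate. That matters most if the result is not significant, when the planned power is part of judging what the trial could have detected.

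**Working it through.** **Inputs.** Control rate 50%, intervention rate 90%, ρ = 0.4, m = 40 and 10 practices per group (all section 3.5); design effect formula (section 3.4). Two-sided alpha of 5% is assumed, since none is stated.

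**Design effect.** D = 1 + 0.4 × 39 = 16.6. Ten practices of 40 give 400 patients per group, or 400 / 16.6 = 24.1 effective patients.

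**Reproducing the stated figure.** Unpooled, the number per group is n = (1.96 + z)² × (p₁q₁ + p₂q₂) / (p₁ – p₂)², and practices per group are n × 16.6 / 40. For 50% against 90%, p₁q₁ + p₂q₂ = 0.25 + 0.09 = 0.34 and (p₁ – p₂)² = 0.16.

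- 90% power (z = 1.2816): n = 10.507 × 0.34 / 0.16 = 22.3, so 9.3 practices per group; with the pooled variance, 10.6.
- 80% power (z = 0.8416): n = 7.849 × 0.34 / 0.16 = 16.7, so 6.9 practices per group; pooled, 8.0; pooled with continuity correction, 10.01.

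The stated 10 per group therefore fits about 90% power without a continuity correction and 80% power with one. The document does not say which was meant.

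**Power of 10 practices per group when usual care improves** (24.1 effective patients per group, no continuity correction):

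| Usual care | Intervention | Power, pooled to unpooled |
|---|---|---|
| 50% | 90% | 88 to 92% |
| 55% | 90% | 80 to 84% |
| 60% | 90% | 68 to 73% |
| 70% | 90% | 41 to 43% |
| 60% | 93.1% | 79 to 84% |

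The last row lets both arms drift by the same odds ratio. Usual care moving from 50% to 60% takes the odds from 1 to 1.5; multiplying the intervention odds of 9 by 1.5 gives 13.5, and 13.5 / 14.5 = 93.1%. With a continuity correction, the 50% and 60% rows against 90% become about 80% and about 55%.

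**Practices needed at 60% against 90%.** Here p₁q₁ + p₂q₂ = 0.24 + 0.09 = 0.33 and (p₁ – p₂)² = 0.09.

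- 80% power: n = 7.849 × 0.33 / 0.09 = 28.8, so 11.9 practices per group unpooled; 13.1 pooled.
- 90% power: n = 10.507 × 0.33 / 0.09 = 38.5, so 16.0 practices per group unpooled; 17.3 pooled.

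**Larger numbers of practices at 60% against 90%.** Sixteen per group give 88 to 90% power; 24 per group give 97 to 98%.

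**The case against.** Several points on the other side have force.

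- **The 60% is not a usual care forecast.** Section 1.6.2 reports it as what patients with CVD and diabetes can achieve under the GMS contract, and its threshold of 5 mmol/l is not clearly the trial's definition of control: Appendix III sets a lower goal after CABG and also asks for a reduction in cholesterol. This stands, so 60% is used only as a scenario.
- **Drift may reach both arms.** Section 1.6.2 ties the improvement to passive dissemination of guidance, which intervention practices also receive. Under equal drift the loss is much smaller (79 to 84% power). This stands too, and the result should be read as a range.
- **More practices may take part.** Forty-nine were invited. If about 32 or more were randomised, power at 60% against 90% would be back at about 90%. The paragraph does not say this, however, and gives dropout as the only reason for the extra invitations.
- **Pairing may help.** Section 3.9 pairs practices on baseline cholesterol control, which may reduce between-practice variation. The design effect of 16.6 gives no credit for it. The gain cannot be quantified from the document.

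Two stronger readings are tempting and are not supported. A reader might infer that the stated size was built for 90% power and for nothing else, but 10 per group also fits 80% power with a continuity correction. A reader might also infer that the design could not see any effect the literature review reports, since section 1.3 says: "The median improvement in prescribing from this approach is estimated to be approximately 6% with a range from -4% to 17" per cent. Those figures concern prescribing, not the proportion of patients with controlled cholesterol, and section 1.4.5 describes a non-randomised study of outreach plus facilitation in which use of the preferred drug rose by 53.8%. The two kinds of effect cannot be compared directly.

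**Conclusion.** The inconsistency between sections 1.6.2 and 3.5 is real: the protocol says that improvement in usual care belongs in the power calculation, and its only calculation leaves it out. The arithmetic of the stated figure is sound on its own inputs; what is at fault is the control rate assumption and the missing alpha and power.

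Relative to 88 to 92% power at 50% against 90%, the consequence for 20 practices runs from modest (80 to 84% with usual care at 55%, or 79 to 84% with equal drift to 60% and 93%) to material (68 to 73% at 60%) to severe (41 to 43% at 70%). These figures assume a two-sided 5% test, the stated intraclass correlation and cluster size, no gain from pairing, no continuity correction and, outside the equal drift case, an intervention rate that stays at 90%. They describe the stated 20 practices. They do not show that the trial as randomised is underpowered, because the protocol does not give the number randomised. This is a point of moderate weight: it should be corrected, and it does not undermine the design or the analysis.

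**What to change.** Restate the sample size paragraph in section 3.5 so that it:

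- gives alpha, sidedness, target power and the formula used, including whether a continuity correction was applied;
- sets usual care at a raised value, for example 60% with 55 to 70% as sensitivity, labelled as an assumption, and says whether the intervention rate is expected to drift as well;
- gives either the practices required (at 60% against 90%, about 12 to 13 per group for 80% power and 16 to 18 for 90%, depending on the variance formula) or the detectable difference for 20 practices and for the number actually randomised;
- notes that about 32 or more randomised practices would restore about 90% power at 60% against 90%, and that pairing on baseline control may add some.

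The cost is protocol wording and a short recalculation. The stated figure for 20 practices becomes less favourable. No extra practices or data are required, and the analysis does not change.

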Subgroup analyses of differences in endpoints between SOS and usual care groups will be defined by the following baseline variables: age, gender, practice level socioeconomic deprivation (≤ median, > median), practice type (single handed or group), patient type (prevalent: known to the practice at baseline or incident: new diagnoses after baseline date), number of co-morbidities (one vs. two or more), presence or absence of IHD, prescribed or not prescribed a statin and cholesterol controlled or uncontrolled at baseline.

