**3.8 Participating practices and patients**

Practices will be asked to identify patients who had confirmed vascular disease. These patients are at ≥ 30% risk of suffering a cardiovascular, cerebrovascular or peripheral vascular event in the next 10 years. In accordance with GG&C Cholesterol Guidelines (Appendix III), this level of risk will be confirmed by the following confirmed diagnoses:

- Myocardial infarction;
- CABG / angioplasty;
- Angina/IHD;
- Angiographic coronary artery disease;
- Stroke/transient ischaemic attack;
- Peripheral ischaemic arterial disease/intermittent claudication;
- Diabetic patients aged over 45years.

A validated computer search of each general practice’s computerised patient record will generate a list of eligible patients. Each patient’s computerized and paper record will then be screened to collect relevant data.

Due to time and resource limitations, a systematic sample of every third eligible patient’s data will be collected in 5 practices with the largest list sizes (12330, 7354, 7215, 7099 and 5616 patients). Therefore, cross sections of data will be collected at baseline. In addition, in all practices, some demographic data (in particular, the “Patient identification number”) may not be available. Both factors preclude longitudinal follow up of all patients. In all practices, data will be collected from each eligible patient’s record, anonymised in the practice and entered onto an ACCESS database.

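### Subgroups by each patient's baseline statin use and cholesterol control need patient linkage that section 3.8 says is not available for everyone, and incident status is not a baseline variable

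*Protocol*

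**What the plan says.** Section 3.5 lists nine subgroup factors: age, sex, practice deprivation, practice type, patient type, co-morbidity count, IHD, statin prescribing and cholesterol control. It says that the subgroups "will be defined by the following baseline variables". The last two factors are patients "prescribed or not prescribed a statin and cholesterol controlled or uncontrolled at baseline". Patient type is defined as "patient type (prevalent: known to the practice at baseline or incident: new diagnoses after baseline date".

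Section 3.3 sets the primary endpoint, cholesterol control, at the level of the individual patient, assessed on average 1.7 years after randomisation.

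Section 3.8 describes the data. Because of limited time and resources, "a systematic sample of every third eligible patient’s data will be collected in 5 practices with the largest list sizes". It goes on: "Therefore, cross sections of data will be collected at baseline". In all practices, "some demographic data (in particular, the “Patient identification number”) may not be available". Its conclusion is: "Both factors preclude longitudinal follow up of all patients". Records are anonymised inside the practice before database entry, and no retained linking key is described.

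Under Blinding in section 3.9, baseline data are collected before allocation, and two blinded researchers collect prescribing and cholesterol outcomes at follow-up. Nothing is said about also taking earlier values from the record at that visit.

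**The concern.** A subgroup by a patient's own baseline state needs two facts about the same person: the state at baseline and the outcome at follow-up. Section 3.5 assumes that both are available. Section 3.8 says that they cannot be brought together for all patients, and neither section says what happens to the rest. An analyst following the protocol would have to use whichever patients happen to link, or leave the analyses out.

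Linked patients are unlikely to be a random subset. Linkage depends on practice size, through the sampling, and on how complete the identifiers are, which may vary by practice. An interaction estimated in that subset describes the patients who could be matched.

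Incident patients raise a second difficulty. They were diagnosed after the baseline date, so they have no record in the baseline cross section and cannot be placed in either level of these two factors from it. Incident status itself is settled after baseline. In SOS practices pharmacists validate and amend disease registers and reinstate overlooked patients (section 4.1.2), while usual-care practices receive no pharmacist-led support (section 4.2). Who appears at follow-up, and under which label, may therefore differ by arm for reasons other than disease.

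**Working it through.** The protocol states no figure for linkage, so there is nothing to reproduce. The check is whether the data in section 3.8 can supply what section 3.5 asks for.

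**Which factors need linkage**

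- Practice deprivation and practice type are practice attributes and need no patient linkage.
- Age and sex can be read or derived at follow-up without a baseline record.
- IHD and co-morbidity count are called baseline variables, and section 3.8 includes diagnoses in the eligibility criteria. Whether they would come from baseline or follow-up records is not stated.
- Statin prescribing and cholesterol control change over time and are also endpoints (section 3.3). Their baseline values must come from the baseline record or from a dated look-back. Only the first is planned, and it needs linkage.
- Patient type turns on "incident: new diagnoses after baseline date", so it is not known at baseline.

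**How much linkage might be possible (illustration only)**

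Three inputs are not in the protocol and are assumed here:

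- *s*, the share of prevalent follow-up patients who come from the five sampled practices: 0.2 to 0.5
- *m*, the share of patients with a missing identifier: 0 to 0.3
- the follow-up sampling scheme in those five practices, which section 3.8 does not describe

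If follow-up there covers all eligible patients or draws a fresh independent sample, the linkable share of prevalent patients is (1 − *s* + *s*/3) × (1 − *m*):

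- *s* = 0.2, *m* = 0: (0.8 + 0.067) × 1 = 0.87
- *s* = 0.5, *m* = 0.3: (0.5 + 0.167) × 0.7 = 0.47

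If the same sampled patients are revisited, the sampling no longer matters and the share is about 1 − *m*:

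- *m* = 0: 1.00
- *m* = 0.3: 0.70

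Under these assumptions the linkable share runs from about 47% to about 100% of prevalent patients. A higher *m* would lower it further, and the protocol sets no bound on *m*. For incident patients the share is zero under every scheme, because they have no record in the trial's baseline data.

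**A classification gap**

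Section 4.1.2 expects that some eligible patients will have been overlooked by their practice and that the pharmacist will put them back on the register. Such a patient is not clearly known to the practice at baseline and is not a new diagnosis either. The section 3.5 definition does not place this patient, and the situation is actively created in one arm only.

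**The case against.** The strongest reply is that these are exploratory subgroups. The primary comparison of follow-up control between arms needs no linkage. Restricting a subgroup to patients with the necessary data is routine and can be left to a statistical analysis plan, which is not at hand. The prevalent and incident definitions are explicit, so calling the factor a baseline variable is mainly a matter of labelling.

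Most of that stands, and it limits the weight of the point. It does not remove it. The protocol itself fixes both the subgroup list and the data structure, and the two do not fit. Writing down a restriction would still leave a selected subset, whereas a dated look-back avoids the selection caused by linkage.

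Several stronger readings are tempting but unsupported:

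- A reader might infer that no linked data will exist. Section 3.8 says only that identifiers may be missing and that follow-up of all patients is precluded. Outside five practices every eligible patient's data are collected, so a linkable remainder is likely.
- A reader might infer that a follow-up patient in a sampled practice has a one-in-three chance of a baseline record. That depends on a follow-up sampling scheme that the protocol does not give.
- A reader might fear subgroups defined by the outcome, with follow-up status standing in for baseline status. The protocol does not propose this.
- A reader might turn this into a multiplicity point. Nine factors by nine endpoints gives 81 contrasts, and 81 × 0.05 is about 4 expected false positives if every null held at an assumed 5% level. That is a separate matter and does not bear on linkage.
- A reader might replace the two factors with practice-level baseline proportions. That asks an ecological question, and the proportion controlled is already the pairing variable (section 3.9).

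**Conclusion.** The point holds in a limited form. Two of the nine subgroup factors, baseline statin prescribing and baseline cholesterol control, cannot be formed for the full follow-up set from the data that section 3.8 describes. They can be formed only for linkable prevalent patients, a subset of unstated size that is unlikely to be random, and for no incident patients. A third factor, patient type, is labelled a baseline variable but is determined after baseline and is open to differential ascertainment between arms.

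This rests on two readings: that the subgroups use each patient's own baseline status, as the wording implies, and that no look-back at the record is intended, since none is described. A practice record may well hold an earlier prescription or cholesterol value, even for an incident patient. The protocol simply does not plan to use it. The size and direction of any bias cannot be derived from the document. Only secondary analyses are affected, so this is an inexpensive improvement and not a threat to the main result.

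**What to change.** 1. At follow-up extraction, have the blinded researchers record two further items for each prevalent patient from the dated practice record: the statin prescription in force, and the last cholesterol result, both as at the practice's randomisation date.
2. Define the statin and cholesterol-control subgroups from those fields, in prevalent patients only, and say so in section 3.5.
3. Remove patient type from the list of baseline variables. Report incident patients as a separate post-randomisation population, noting that register validation and case finding in the SOS arm may have affected who was identified.
4. Align the cut-off. Section 3.5 defines incident by the baseline date, while the new fields use the randomisation date, so the plan should say where a patient diagnosed between the two belongs.

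The cost is wording plus two dated fields per patient. Some patients will have no cholesterol recorded before randomisation, and their number should be reported by arm. The look-back removes the dependence on identifiers and on the baseline sampling. It does not remove any effect of SOS case finding on which prevalent patients are on the list at follow-up, and that should be stated as a limitation.
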